#### Treatment as usual (TAU)

TAU is defined as the routine care that participants receive when treated for a depression or anxiety disorder in outpatient mental healthcare. The type of treatment may vary, and may include all evidence-based types of psychotherapy that are part of the treatment guidelines for depression and anxiety disorders – combined with pharmacotherapy, if necessary. TAU will mainly consist of Cognitive Behavioral Therapy (CBT) [53] or Interpersonal Psychotherapy (IPT) [54], often combined with antidepressant medication. TAU will be offered at each participating site, and will not be interfered with during the study in both the experimental group and the control group. TAU may be offered individually or in a group, and face-to-face, online, or blended. We will closely monitor the type and amount of treatment through patient records, the patient’s self-reported health care utilization, and a therapist questionnaire.

#### iERT-therapists

iERT will be provided by therapists of the e-mental health clinic of GGZ inGeest, who have ample experience with delivering internet-based treatment for depression. All therapists will receive an extensive training on how to deliver iERT – including how to use the online intervention and how to provide written feedback within the theoretical framework of ART. In order to ensure treatment fidelity, a detailed treatment manual with standardized written feedback templates will be available to guide therapists through the iERT-treatment. In addition, iERT-therapists will regularly receive supervision. A random sample of each therapist’s written feedback will be analyzed and discussed in supervision sessions. For all patients, the iERT-therapist will be a different therapist than their TAU-therapist. Prior to iERT, the TAU-therapist provides necessary information regarding the patient’s diagnosis and treatment progress to the iERT-therapist – a procedure for which the patient has provided written consent.

### Primary outcome measure

#### Violent victimization

Violent victimization will be measured with section 4 of the Safety Monitor (Dutch version: Veiligheidsmonitor) [55], which is developed by the Dutch Ministry of Security and Justice. The Safety Monitor strongly resembles the International Crime Victimization Survey (ICVS) [56] and is used by Statistics Netherlands (CBS) to measure victimization annually on a large scale. The Safety Monitor is an adequate self-report instrument that assesses victimization of 11 different crimes, subdivided into three categories: violent crimes, property crimes, and vandalism. In this study, we will only assess the violent crimes category, which consists of three subcategories: physical assault, sexual assault, and threat. Physical assault will be defined as deliberately hurting a person physically, with or without the use of a weapon. Sexual assault will be defined as unwanted sexual touching. Lastly, threat will be defined as threatening to hurt a person physically or sexually, without using actual violence. For each of these crimes, participants are asked whether they have become victim of that crime in the past 5 years. If so, participants are asked whether they have experienced that crime in the past 12 months, and, when answering affirmative, how frequently they experienced that crime in the past 12 months. The primary outcome measure is the total number of violent victimization incidents at 12 months after baseline (T4).

### Key secondary outcome measures

#### Diagnosis of depression

The presence of a current and lifetime diagnosis of depression in the past and present will be assessed with section A and B of the MINI International Neuropsychiatric Interview (MINI; version 5.0) [50]. The MINI is a structured, clinician-administered diagnostic interview that is widely used to assess the presence of psychiatric disorders based on the Diagnostic and Statistical Manual of Mental Disorders (Fourth edition; DSM-IV) and the International Classification of Diseases (Tenth revision; ICD-10). The MINI demonstrated a good Kappa score of 0.84 in diagnosing MDD, with a sensitivity of 0.96 and a specificity of 0.88 in comparison with the patient-rated version of the Structured Clinical Interview for DSM-IV (SCID) [57]. The validated Dutch version of the MINI [58] will be used.

At T0, sections A and B of the MINI will be conducted to assess current and lifetime depression. In addition, sections C, D, I, J, K, and L of the MINI will be administered to assess the presence of suicidality, bipolar disorders, posttraumatic stress disorder, alcohol abuse or dependency, drug abuse or dependency, and psychotic disorders, respectively. At T4, section A will be administered again in a telephone interview, to determine remission rates of depression. In addition, the sections covering suicidality, posttraumatic stress disorder, and alcohol and drug abuse or dependency will be administered again.

#### Depressive symptom severity

Depressive symptoms will be assessed with the 30-item Inventory of Depressive Symptomatology – Self Report (IDS-SR; Dutch translation) [59, 60], which is a self-report questionnaire designed to measure depressive symptom severity. The IDS-SR includes all diagnostic DSM-IV criteria for major depressive disorder (MDD), as well as melancholic, atypical, and commonly associated symptoms for MDD (e.g., anxious mood, irritable mood). The IDS-SR covers five core symptom domains: vegetative symptoms, cognitive changes, mood disturbance, endogenous symptoms, and anxiety symptoms. All items are rated on a 4-point Likert scale from 0 to 3, and are equally weighted in the total score. The IDS-SR has highly acceptable psychometric properties and has been demonstrated to be sensitive to treatment effects in depressed outpatients [60–62]. The IDS-SR will also be used to determine response and remission rates. Response rates will be defined as a reduction in baseline total score of the IDS-SR of at least 50%. Remission rates will be defined as the absence of a diagnosis of depression according to the MINI and an IDS-SR score of < 18 [60].

### Other secondary outcome measures

Other secondary outcome measures are:Quality of life, as measured with the EuroQol 5D (EQ-5D-5 L) [63];Healthcare costs and productivity losses/gains, as measured with the Trimbos/iMTA questionnaireon Costs associated with Psychiatric illness (TiC-P) [64];Psychopathology, as measured with the Brief Symptom Inventory (BSI) [65];PTSD symptomatology, as measured with the Posttraumatic Diagnostic Scale (PDS) [66];Interpersonal functioning, as measured with the Inventory of Interpersonal Problems (IIP-C) [67];Coping style, as measured with the subscales *Active tackling* and *Avoidance* of the Utrecht Coping List (UCL) [68].

### Process variables

#### Emotion dysregulation

Emotion dysregulation will be measured with the Difficulties in Emotion Regulation Scale (DERS) [69]. The DERS is a 36-item self-report scale that assesses clinically relevant emotion regulation difficulties across various dimensions, represented in six subscales: non-acceptance of emotional responses, difficulty engaging in goal-directed behavior, impulse control difficulties, lack of emotional awareness, limited access to emotion regulation strategies, and lack of emotional clarity. The DERS has demonstrated high internal consistency, good test-retest reliability [69–71], and adequate construct and predictive validity [69].

#### Positive and negative affect

The 20-item Positive and Negative Affect Schedule (PANAS) [72] will be used to assess positive and negative affect at the time of assessment; both represented by 10 items that are rated on a 5-point Likert scale. Each item consists of an affective state, such as “excited”, “proud”, and “attentive” for the positive affect subscale, and “distressed”, “ashamed”, and “guilty” for the negative affect subscale. The PANAS has good internal consistency and validity [72]. The Dutch version [73] yields acceptable to good psychometric properties as well, with a Cronbach’s alpha of .77 and .87 for the positive and negative affect subscales, respectively [74].

#### Sad mood

Sad mood will be measured by a digital version of the 1-item Visual Analogue Mood Scale (VAMS), which consists of a line that runs from zero to 100, with the descriptors “happy” located on the left side and “sad” on the right side. A higher score represents a sadder mood. Patients are asked to rate their current mood by placing a cursor on the line, with the following instruction: “You can answer the following question by replacing a cursor on the line from 0 to 100. At this moment, I feel…”. The VAMS has been used previously in studies examining the influence of sad mood on relapse and recurrence of depression [75, 76]. In the experimental condition, the VAMS will be assessed after each iERT-session as well.

#### Brooding

The 5-item Brooding subscale of the Ruminative Response Scale (RRS; Dutch version) [77, 78] assesses the dysfunctional thinking pattern of drawing one’s attention to problems and their consequences. For each item, respondents are asked to rate the extent to which it reflects their responses to sadness on a 5-point Likert scale. An exemplary item is “I think: why do I always react this way?”. The Brooding subscale has satisfactory internal consistency (Cronbach’s alpha = .77) [77] and predicted depression both cross-sectionally [79] and prospectively [77].

#### Dysfunctional attitudes

The Dysfunctional Attitude Scale form A (DAS-A) is a self-report scale designed to measure patterns of negative thinking in depressed patients [80], with good internal consistency and validity [81–83]. In this study, the shorter 17-item version will be used (DAS-A-17). Respondents are asked to what extent they agree with each of 17 dysfunctional assumptions on a 7-point Likert scale. A confirmatory factor analysis demonstrated the Dutch version of the DAS-A-17 to yield good psychometric properties in terms of reliability and convergent construct validity [84]. 

#### Sense of control

Sense of control is measured with the 7-item Mastery scale [85]. Mastery concerns the extent to which one perceives oneself to be in control of events and factors that influence one’s life [85]. Respondents are asked to rate the extent to which they agree with seven statements on a 5-point Likert scale, for example: “There is really no way that I can solve some of the problems that I have.” The Mastery scale has adequate psychometric properties [85, 86].

### Potential moderators

Demographic characteristics, collected at baseline;Childhood trauma, as measured with the Childhood Trauma Questionnaire (CTQ) [87];Alcohol and drug abuse or dependency, as measured with the MINI 5.0 [50];Self-esteem, as measured with the Self-Esteem Rating Scale Short-Form (SERS-SF) [88];Personality dimensions, as measured with the Neuroticism-Extraversion-Openness Five Factor Inventory (NEO-FFI) [89];Negative life events, as measured with the List of Threatening Experiences [90];Working alliance, as measured with the Working Alliance Inventory – Short Form (WAI-SF) [91].

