#### Randomization and procedure

Randomization will be carried out after completion of the first part of the baseline assessment. Randomization of participants in every participating site will be performed by a research associate of the data management department of GGZ inGeest, who is not familiar with the subject, nor involved in providing any kind of mental health care. Randomization will take place at an individual level, stratified by mental health care site, using a computer-generated block randomization schedule. To ensure that an equal number of patients will be allocated to TAU and TAU + iERT, the allocation ratio will be 1:1. To prevent selection bias, researchers and outcome assessors will be blind to block size and order, and will not have access to the randomization schedule. Due to the nature of treatments, blinding of participants and therapists to treatment condition is not feasible. Blinding research assistants to treatment allocation is not applicable to most outcome measures, since these will be administered online. Research assistants responsible for administering the MINI interview by telephone at 12 months after baseline will be blinded to treatment allocation. To promote data quality, all research assistants will be trained in administering the MINI interview. Audio recordings will be made of every MINI interview, which will be used in supervision sessions. Since all other measures concern web-based questionnaires that are filled out by the participants themselves, double data entry procedures are not applicable.

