During the treatment phase, assessments will be administered at 8 weeks, 14 weeks, and 6 months after start of TAU in both the experimental and the control group. Follow-up assessments will be administered at 12, 24, and 36 months after the first baseline assessment. Except for the MINI, which will be assessed in a telephone interview at 12 months after baseline, all assessments will be conducted online. Patients receive an e-mail with a link to the self-report questionnaires, and those who have not completed an assessment within 4 days will receive a reminder via e-mail. Patients who have not completed the assessments after one week will be approached via telephone by a research assistant. If necessary, online assessments can also be completed over the telephone by an assistant who is blinded to treatment condition. Participants will be compensated with a voucher of 15 euros per assessment for both the first and second part of T0, T1, T2, T3, T5 and T6, and a voucher of 30 euros for T4.

Additional questionnaires will be sent out in the TAU + iERT condition: a visual analogue mood scale (VAMS) is to be completed online after every iERT-session in the online treatment platform, and the System Usability Scale (SUS) and Technical Alliance Inventory (TAI) are to be filled out after completion of iERT. The SUS will also be sent out once to each iERT-therapist. Table 1 provides an overview of all instruments per assessment.

**Table 1 Tab1:** Overview of instruments per assessment

Instrument	T0_1_	T0_2_	T1	T2	T3	T4	T5	T6^a^
Mini International Neuropsychiatric Interview	x					x		
Safety Monitor	x					x	x	x
Inventory of Depressive Symptomatology	x		x	x	x	x	x	x
Difficulties in Emotion Regulation Scale	x		x	x	x	x	x	x
Visual Analogue Mood Scale	x		x^b^	x	x	x	x	x
Positive and Negative Affect Schedule	x		x	x	x	x		
Demographic questionnaire	x							
Posttraumatic Diagnostic Scale		x			x			
Childhood Trauma Questionnaire	x							
List of Threatening Experiences		x						
Brief Symptom Inventory		x			x			
Utrechts Coping List		x				x		
Ruminative Response Scale		x	x	x	x	x		
Pearlin Mastery Scale		x	x	x	x	x		
Dysfunctional Attitude Scale		x	x	x	x	x		
Self-Esteem Rating Scale	x							
Inventory of Interpersonal Problems		x				x		
NEO Five Factor Inventory			x					
EuroQol 5D-5 L	x				x	x		
Trimbos questionnaire on Costs associated with Psychiatric Illness	x				x	x		
Working Alliance Inventory				x				
Client Satisfaction Questionnaire				x				

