Technical Alliance Inventory				x^c^				
System Usability Scale				x^c^				

^a^*T0*_*1*_*:* baseline part 1, *T0*_*2*_*:* baseline part 2, *T1:* 8 weeks after start of TAU, *T2:* 14 weeks after start of TAU, *T3:* 6 months after start of TAU, *T4:* 12 months after baseline, *T5:* 24 months after baseline, *T6:* 36 months after baseline

^b^Will also be assessed after each iERT-session in the experimental group

^c^Will only be assessed in the experimental group

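### Two of the seven potential moderators, personality and working alliance, are first measured after randomisation and during treatment, so effect-modification analyses that use them may be biased

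*Protocol article*

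**What the plan says.** The section Potential moderators names seven variables. Five are demographic characteristics, childhood trauma, substance abuse or dependency, self-esteem and negative life events. The other two are personality, measured with the NEO-FFI, and "Working alliance, as measured with the Working Alliance Inventory" in its short form.

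In Table 1 the row "NEO Five Factor Inventory" has one mark, under T1, and the row "Working Alliance Inventory" has one mark, under T2. The table notes define T1 as "8 weeks after start of TAU" and T2 as "14 weeks after start of TAU". The section Randomization and procedure places both in the treatment phase: "During the treatment phase, assessments will be administered at 8 weeks, 14 weeks, and 6 months after start of TAU". The same section fixes the time of allocation: "Randomization will be carried out after completion of the first part of the baseline assessment". No other section gives an earlier NEO-FFI or working alliance measurement.

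Moderators belong to the stated aims (Abstract, Research aims), and the Discussion presents them as part of what the design offers.

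**The concern.** A moderator analysis asks whether a characteristic that patients had before allocation changes the effect of iERT. Randomisation balances such characteristics, so the arms can be compared at each level of them. A score first taken during treatment lacks that protection. If allocation has changed it, patients with the same score in the two arms are no longer comparable, and an apparent moderation may be a consequence of treatment.

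Both variables are open to this. iERT targets emotion regulation, and self-rated personality in depressed patients may move with mood. Working alliance cannot exist before therapy begins. In the TAU + iERT arm the iERT therapist differs from the TAU therapist (section iERT-therapists), and the article does not say which of them the patient rates, so the score may not mean the same thing in both arms.

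At stake is a secondary, exploratory aim. For personality the loss would be permanent: if the NEO-FFI is collected only at T1, no later analysis plan can recover a baseline score.

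**Working it through.** The article states no figure to reproduce. The check sets the schedule against the time of randomisation and then asks when bias follows.

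**Step 1. Timing of each listed moderator (Table 1; Randomization and procedure).** Five single-mark rows (NEO-FFI, Working Alliance Inventory, CTQ, Self-Esteem Rating Scale, List of Threatening Experiences) were counted cell by cell. Each has eight time cells, so the marks align with the columns.

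| Moderator | Instrument | First measured | Relative to randomisation |
|---|---|---|---|
| Demographics | questionnaire | T0_1 | before |
| Childhood trauma | CTQ | T0_1 | before |
| Alcohol and drug abuse | MINI | T0_1 | before |
| Self-esteem | SERS-SF | T0_1 | before |
| Negative life events | List of Threatening Experiences | T0_2 | after the trigger, with the baseline questionnaires |
| Personality | NEO-FFI | T1 | after, in the treatment phase |
| Working alliance | WAI-SF | T2 | after, in the treatment phase |

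Four are clearly pre-randomisation, one is scheduled after the trigger but with baseline, and two are first measured during treatment: 4 + 1 + 2 = 7.

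**Step 2. Possible iERT exposure by then.** iERT has six sessions, starts after the fourth TAU session, and opens at most one session a week, provided the previous one is completed. TAU frequency is not stated, so the following rests on an assumption.

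- Weekly TAU, iERT from about week 4: sessions open at weeks 4, 5, 6, 7, 8 and 9. About four precede T1 (week 8) and all six can precede T2 (week 14).
- Fortnightly TAU, iERT from about week 8: sessions open at weeks 8 to 13. About none precede T1, and up to six can precede T2.

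Exposure before the NEO-FFI thus ranges from about none to about four sessions. In either case both instruments are completed after allocation by participants who are not blinded.

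**Step 3. When a shifted score biases an interaction.** Let A be arm (0 or 1), M0 the true baseline score and M1 the measured score. Suppose log rate = α + βA + γM0 + δA·M0.

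If treatment moves every score by the same amount, M1 = M0 − cA, then M0 = M1 + cA. Because A² = A, substitution gives

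log rate = α + [β + (γ + δ)c]A + γM1 + δA·M1.

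The interaction δ is unchanged. A uniform shift therefore does not bias it; bias requires the shift to vary with individual benefit.

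**Step 4. Illustration by simulation (assumed inputs).** N = 200, allocated 1:1. The control rate is 3.0 at M0 = 0, with gamma overdispersion of variance 1. M0 is standard normal with γ = 0.2 and no true interaction. Individual benefit b, on the log-rate scale, is normal with mean log(1/0.7) = 0.357 and SD 0.5, independent of M0. The measured score is M1 = M0 − k·b·A. The model is a Poisson regression with robust standard errors and an arm-by-moderator term, 1,000 runs per row.

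| k (SD per unit of benefit) | Mean shift, k × 0.357 | Baseline score: coefficient, rejected | Post-randomisation score: coefficient, rejected |
|---|---|---|---|
| 0.25 | 0.09 SD | 0.00, 6.9% | 0.06, 7.9% |
| 0.5 | 0.18 SD | 0.00, 7.9% | 0.11, 12.1% |
| 1.0 | 0.36 SD | 0.00, 7.0% | 0.16, 18.4% |

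At N = 20,000 (20 runs per row) the spurious coefficients remain at 0.06, 0.10 and 0.16, so a larger sample does not remove them. The simulation shows the mechanism under a shift tied entirely to benefit. It does not estimate the bias in this trial.

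**The case against.** The strongest reply is that the article proposes no test that could be biased. The section Data analysis describes mixed models for effectiveness and multilevel mediation models, but no moderator model. The variables are called only potential moderators, and their analysis may properly be left to an analysis plan not shown here. That is fair as to the model. It does not settle the point, because the article itself fixes both the role and the measurement time, and these do not fit together.

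A reader might infer that interactions with these variables would necessarily be biased. The document does not support that. Bias needs a shift related to individual benefit (Step 3), and with the smallest assumed shift the rejection rate is 7.9% against 6.9% for the baseline score, practically no difference. If NEO-FFI scores are stable under treatment, the bias may be negligible.

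A reader might also infer that the results are meant to select patients for iERT, or that the alliance score includes the iERT therapist. The article says neither.

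Finally, if a moderator must precede randomisation, the List of Threatening Experiences at T0_2 also falls short. That stands. It is a milder case, since it is scheduled with the baseline questionnaires and not with the treatment-phase assessments.

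**Conclusion.** The point holds as a conflict between stated role and stated schedule. Two of seven listed moderators are first measured after randomisation and in the treatment phase, and a third is scheduled after the randomisation trigger but alongside baseline. The timing is exact and rests on no assumption.

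The consequence is conditional: effect-modification analyses using these scores may be biased, to an unknown extent and in an unknown direction, if allocation alters the scores in a way related to benefit. The simulated figures depend on assumed inputs and serve only as illustration.

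The two cases differ. Personality could have been measured before allocation. Working alliance could not, and is by nature a process variable. The primary comparison of victimisation incidents does not use these variables and is unaffected.

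**What to change.** - Collect the NEO-FFI in baseline part 1 (T0_1). Part 2 is suitable only if randomisation is moved to follow it.
- Take working alliance off the moderator list, analyse it as a process variable or within-arm predictor, and state which therapist is rated in the TAU + iERT arm.
- For patients without a pre-randomisation NEO-FFI, report the analysis as associational only.
- Move the List of Threatening Experiences to T0_1, or flag that it is collected after the randomisation trigger.

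The cost is a slightly longer baseline part 1, with T1 shortened by the length of the NEO-FFI, and a few lines of wording. Moving randomisation after part 2 instead would delay allocation until part 2 is complete, preferably within a week of part 1 under the current schedule.
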